### Recruitment of study population

Recruitment began on 1 January 2019 and is expected to be complete within 36 months (31 December 2021). Participants present on surgical lists will be recruited from the emergency department (ED), the cardiovascular wards or cardiac ICU depending on the coordinating center. Patients transferred directly to the OR will be recruited in the ED. Patients transferred to the cardiac ICU or ward under sedation and blood pressure control will be recruited in the ICU. The surgery need not be postponed for obtaining consent, even if the patient is transferred directly to the OR. If a patient with AAAD in the ED requires emergency surgery, the surgical fellow will be informed and will inform the anesthesiologist, research assessors and perfusionist to obtain the relevant consents in the ED.

After surgical consent is obtained by surgical fellows, a researcher will clearly explain to patients or their relatives sufficient information about this trial, including the benefits and drawbacks associated with participation. Simple language will be used to facilitate the understanding of medical terms. Participants who give consent will provide demographic and general medical data as described below in the section “Baseline study visit.”

The target study population is all patients aged 18 years or older diagnosed with AAAD and scheduled for elective or emergency TARS under CPB. Patients are eligible for the study if they are older than 18 years old and show AAAD on contrast computed tomography. Patients will be excluded from the study if they are unable to understand or give informed consent, if they are pregnant or if they are already participating in another clinical trial that might interfere with the primary or secondary outcomes of the present trial. Patients will also be excluded if they have had a hemi-arch replacement or if they or their relatives revoke consent. Patients can leave the study at any time for any reason if they wish to do so without any consequences. Patients who withdraw from the study will not be replaced. Withdrawals will be documented in the electronic case report form (eCRF). The investigator can decide to withdraw a participant from the study for urgent medical reasons.

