### Randomization and blinding

Patients will be randomly assigned to either the RIVP group or the control group by an independent statistician uninvolved in the trial using a computer-generated randomization list. The randomization will take place upon entry into the operating room (OR). The study is designed such that the outcome assessor and patient will be blinded. The principal investigator at each center will reveal the randomization to the perfusionist but will not perform the perfusion or collect or analyze the data. The perfusionist will perform RIVP, record RIVP data, and input the data into the eCRF. The outcome assessor will obtain informed consent and collect preoperative as well as postoperative follow-up data. These data will be input into the eCRF by the data manager, who will log in using his or her own account information and who will be unable to access data input by the perfusionist. The statistician will see the two groups only as groups 1 and 2. The surgeon, perfusionist, and anesthesiologist will not be blinded to patient allocation because of the need to perform the corresponding procedures correctly. In cases when exclusion criteria are met after randomization (e.g., if total arch replacement is not performed), the patient will be withdrawn from the trial but will retain his or her identification code (randomization number).

Since the treatment allocation involves a surgical procedure, the surgeon, perfusionist, anesthesiologist, and other OR personnel will not be blinded to patient allocation. The perfusionist will record the intraoperative data. The assessor will be responsible for collecting preoperative data and obtaining informed consent, as well as for conducting postoperative visits. Physicians interacting with patients outside the OR will be blinded to treatment allocation. The details of the randomization will be kept confidential until completion of data analysis.

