### Sample size calculation

The sample size was calculated based on the primary outcome of our unpublished pilot study (manuscript in preparation), carried out at West China Hospital (Biomedical Ethics Committee approval no. 201824). In this study, we included 76 patients (*n* = 38 in each group), and defined the primary outcome as the abovementioned 30-day composite of operative mortality and major complications. In this pilot study, 13 of 38 control patients (34.2%) suffered the following outcomes: death, 4; paraplegia, 1; postoperative renal failure, 7; severe liver dysfunction, 4; or gastrointestinal complications, 1. A total of 9 of 38 patients in the RIVP group (23.7%) experienced the following outcomes: death, 3; paraplegia, 0; postoperative renal failure, 6; severe liver dysfunction, 1; or gastrointestinal complications, 1. The trial is planned to have 80% test power with a two-sided type I error rate of 5%, assuming a dropout rate of 10% over the course of the entire study. For statistical significance, 636 patients (318 participants in each arm) will be required for this trial according to the following statistical formula not including the 76 patients in the pilot study:$$ \mathrm{n}=\frac{{\left({Z}_{1-\alpha /2}+{Z}_{1-\beta}\right)}^2\left[{p}_1\left(1-{p}_1\right)+{p}_2\left(1-{p}_2\right)\right]}{\delta^2} $$

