### Data analysis

All patients will be analyzed according to the intention-to-treat protocol. Data analysis will be performed by a statistician using SPSS 20.0 (IBM, Chicago, IL, USA). Differences associated with *p* < 0.05 will be considered statistically significant. Continuous variables will be expressed as mean ± standard deviation or median (interquartile range), and differences in such variables will be analyzed using an independent *t* test or the Wilcoxon signed-rank test, depending on whether data are normally distributed. Categorical variables will be described as numbers (percentages), and differences in such variables will be analyzed using a *chi-square test* and *Fisher’s exact test*. *Kaplan-Meier* curves and *log-rank* analysis will be used to compare inter-group differences in primary and secondary outcomes. Univariate and multivariate logistic regression will be performed to determine relative risk of primary and secondary outcomes in the RIVP group compared with the control group.

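### The rule withdrawing randomized patients who do not get a total arch replacement conflicts with the promised intention-to-treat analysis and can remove primary events selectively

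*Protocol article*

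**What the plan says.** All places are in the Methods of the protocol article.

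- **Data analysis** (and, in the same sense, the abstract): "All patients will be analyzed according to the intention-to-treat protocol".
- **Randomization and blinding**, on timing: "The randomization will take place upon entry into the operating room (OR"). The same section says twice that the surgeon, perfusionist and anesthesiologist are not blinded.
- **Randomization and blinding**, on patients who turn out to meet an exclusion criterion once they have been randomized, with this example: "if total arch replacement is not performed), the patient will be withdrawn from the trial". The identification code is the only item mentioned as kept. Nothing is said about following these patients or counting them.
- **Recruitment of study population**: "Patients will also be excluded if they have had a hemi-arch replacement or if they or their relatives revoke consent". Withdrawn patients are not replaced, and withdrawals are documented in the eCRF. A further clause reads: "The investigator can decide to withdraw a participant from the study for urgent medical reasons". It has no time point.
- **Study outcomes**: death in the hospital where the operation took place counts as operative mortality, which is part of the primary composite.
- **Sample size calculation**: 318 per arm, "assuming a dropout rate of 10% over the course of the entire study".

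**The concern.** Intention-to-treat keeps each randomized patient in the allocated arm whatever is done afterwards. The withdrawal rule applies explicitly after randomization and depends on which operation was performed. Three features of the design make this more than a matter of wording.

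1. Patients are randomized before the chest is opened, so the operation can still depart from the plan after allocation.
2. Whether a total arch replacement is completed is settled in the operating room by staff who know the allocation.
3. A patient who dies on the table before the arch is replaced has had no total arch replacement. Read literally, the rule withdraws that patient, although the death is a primary event.

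If the rule is applied as written and withdrawn patients are then left out, the arms compared are no longer those created by randomization. Events can be lost unequally between them.

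**Working it through.** **The plan's own figure.** The inputs are p1 = 0.342 (13/38), p2 = 0.237 (9/38), two-sided 5% and 80% power. The article's formula gives

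n = 7.849 × (0.342 × 0.658 + 0.237 × 0.763) / 0.105² = 7.849 × 0.40587 / 0.011025 = 288.9, so 289 per arm.

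289 × 1.10 = 317.9, so 318 per arm and 636 in total. The stated size is reproduced, so the point concerns who is analysed and not the arithmetic.

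**Side by side.** One section requires all patients to be analysed as randomized. Another takes a defined group of randomized patients out of the trial. No section says that their outcomes are still collected or counted. A team following the second instruction literally would not have the data to carry out the first.

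**How large the bias could be.** The article gives no rate of operations short of a total arch replacement. The withdrawal fraction w and the event rate q among those withdrawn are therefore my assumptions. Take no true effect, p = 0.342 in both arms, 318 randomized per arm, and withdrawals from the RIVP arm only.

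- Observed RIVP rate: p_R = (p − w·q) / (1 − w)
- Standard error: SE = √[p(1 − p)/318 + p_R(1 − p_R)/(318(1 − w))]
- Chance of a significant result favouring RIVP: Φ((p − p_R)/SE − 1.96)

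| w (patients) | q | p_R | Spurious difference | False win for RIVP |
|---|---|---|---|---|
| any | 34.2% | 34.2% | 0 | 2.5% |
| 3% (about 10) | 60% | 33.4% | 0.8 points | 4.0% |
| 5% (about 16) | 60% | 32.8% | 1.4 points | 5.5% |
| 3% (about 10) | 100% | 32.2% | 2.0 points | 7.8% |
| 5% (about 16) | 100% | 30.7% | 3.5 points | 15.0% |

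Worked line for w = 5%, q = 100%: p_R = (0.342 − 0.05)/0.95 = 0.3074. The difference is 0.0346, SE = 0.0376, and Φ(0.922 − 1.96) = 0.150. That spurious difference is a third of the planned 10.5 points.

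**What keeping everyone costs.** Suppose all 318 per arm are analysed and a fraction u gets no benefit from allocation, with a 34.2% event rate in those patients. The difference becomes (1 − u) × 10.5 points. With the unpooled variance, as in the article's formula:

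- u = 0: 10.5 points, power 83.6%
- u = 5%: 9.98 points, power 79.5%
- u = 10%: 9.45 points, power 74.8%

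**The case against.** **Silence is not exclusion.** The text never says outright that withdrawn patients leave the analysis. They keep their randomization number, are not replaced and are logged in the eCRF, and ongoing severe adverse events are followed to a final outcome. All of this is compatible with intention-to-treat, and a full protocol or SAP may define the analysis sets. This stands as a limit: a reader might infer that the primary analysis will not be intention-to-treat, and the article does not establish that. It does not remove the conflict, because the article states a rule that cannot be squared with its stated analysis. This is not a detail left to another document.

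**The clause on urgent medical reasons is weak evidence.** It sits in the recruitment section, has no time point, and may mean only leaving study procedures. A reader might infer that it takes out the sickest patients. The text does not say so. It needs clarifying, but the point does not rest on it.

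**The bias figures are chosen.** Withdrawal from one arm only, with every withdrawn patient having an event, is a worst case. Patients are already scheduled for total arch replacement, and the article does not say how often that changes. Losing events from the control arm would bias against RIVP, and withdrawal unrelated to arm or outcome causes no bias. This is correct, and is why a range is shown.

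**The power shortfall is conditional.** A reader might conclude that intention-to-treat means the planned 80% is not delivered. That would need all of the 10% dropout to be patients who are followed but untreated, and the article does not define dropout. Revoked consent or loss to follow-up leaves outcomes missing under any analysis, so the allowance is not an error.

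**Moving randomization later** might seem the natural cure. It is a debatable design choice, since recruitment began in January 2019 and a change would create two regimes within one trial. It would also not close the gap, because the arch is resected after the arms diverge and the course of the operation could still change then.

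**Conclusion.** The point holds in this form: the post-randomization withdrawal rule and the intention-to-treat commitment cannot both be followed as written. Because operating-room staff are unblinded and in-hospital death is a primary event, following the rule literally can remove primary events selectively.

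The direction and size of the bias cannot be derived from the article. On the stated assumptions (no true effect, loss from the RIVP arm only, 3% to 5% withdrawn), the chance of a false win for RIVP lies between about 4.0% and 15.0%, against 2.5% nominal. The upper end needs every withdrawn patient to have had an event. Since the conflict decides who counts in the primary comparison, it should be resolved before any analysis.

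**What to change.** Reconcile the recruitment, randomization and data analysis sections by stating that:

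1. every randomized patient is followed for the primary outcome and analysed in the allocated arm, whatever operation is performed and including death during the operation;
2. withdrawal, whether because total arch replacement was not performed or for urgent medical reasons, means stopping study procedures, and data collection ends only if consent to it is revoked;
3. the comparison restricted to patients in whom total arch replacement was performed is a sensitivity analysis.

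This leaves clinical decisions about the operation untouched. It takes a short amendment and continued outcome collection in the patients concerned, with no change to the 636. The statistical cost is slight dilution: power is about 80% if 5% of patients get no benefit from allocation and about 75% if 10% do. Patients already withdrawn since recruitment opened should have their primary outcome retrieved where consent allows.

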### Experimental intervention protocol

Patients will receive standard general anesthesia induction and maintenance with propofol, sevoflurane, sulfentanil, and muscle relaxants. All patients will be ventilated with a standard protocol (continuous mandatory ventilation, PCO_2_ 35–45 mmHg). Invasive blood pressures in the bilateral radial arteries, left dorsalis pedis artery, central venous pressure, and nasopharyngeal and rectal temperatures will be monitored. In addition, cerebral perfusion will be monitored using near-infrared spectroscopy (NIRS) throughout the surgery. Initial baseline cerebral tissue oxygen saturation will be obtained before anesthesia induction. A transesophageal echocardiographic probe will be routinely placed and used for confirmation of the diagnosis and assessment of cardiac function. A 1-mg/kg bolus of methylprednisolone will also be given.

The operations will be performed via a median sternotomy. After systemic heparinization (400 IU/kg), arterial cannulation (varied by surgeon preference using a central (distal ascending aorta, aortic arch, right axillary, or innominate arteries) or a peripheral (femoral artery) site for arterial cannulation under the guidance of ultrasound) and central cannulations of the superior and inferior venae cavae will be performed. The CPB circuit consists of a membrane oxygenator, a heat exchanger, and two rolling pumps, which can bifurcate the arterial line for both arterial perfusion and inferior vena caval perfusion as necessary [36]. The CPB will be primed with 1600–1800 mL solution (colloid and crystalloid in a 2:1 ratio with 5000 units of heparin). Systemic cooling will be initiated after CPB onset. CPB will be performed with a flow of 2.0–2.8 L/kg/min which will be adjusted to maintain a mixed venous oxygen saturation at around 85%. After the ascending aorta has been cross-clamped, cardiac arrest will be achieved with an infusion of cold-blood cardioplegia delivered in either antegrade or retrograde modes intermittently every 20 min. Acid-base balance will be maintained with the pH-stat method and a conventional modified ultrafiltration will be utilized during CPB.

During the cooling-down process, aortic root procedures, including repair of the aortic valve, or the Bentall procedure for severe aortic regurgitation and dilation of the aortic root, will be performed. Patients will undergo coronary artery bypass grafting if the coronary arteries are involved.

Patients will be systemically cooled to target nasopharyngeal temperature of 24–26 °C and target rectal temperature of 25–28 °C, then ACP or ACP + RIVP will be performed. For all patients, ACP will be established in a pressure-controlled manner (targeted pump pressure of 50–70 mmHg) using axillary cannulation, direct innominate artery cannulation, or left common carotid artery (flow rate at 5 to 10 mL/kg/min) to keep NIRS within 20% of baseline (over 50%). When the NIRS values decrease to < 50% or less than 80% of baseline, bilateral common carotid artery perfusion will be applied. At the initiation of ACP, the supra-aortic vessels will be gently clamped while the ascending aortic clamp and the aortic cannula are removed.

In control patients, only ACP will be performed and the lower body will not be perfused. In ACP + RIVP-group patients, RIVP will also be performed besides ACP. To achieve RIVP, the pump will be connected with the arterial line and inferior vena caval drainage to drive the blood from the arterial line to the inferior vena cava by cross-clamping of the drainage and placement of snares around the inferior vena caval cannula. RIVP will be performed at a flow rate of 5–12 mL/min/kg and perfusion pressure below 25 mmHg. Ascites can occur when capillary pressures are above this perfusion pressure cut-off [30]. During RIVP, an additional sucker will be then introduced into the proximal descending aorta to capture blood return during the reconstruction of the open distal anastomosis to maintain a bloodless field after the opening of the aortic arch.

During MHCA or RIVP, the arch will be resected distally to the orifice of the left subclavian artery with each head vessel prepared for individual anastomosis. A stent endograft (frozen elephant trunk) will be inserted into the true lumen of the descending aorta in an antegrade manner under direct vision. Then the aortic wall will be anastomosed to a four-branched graft end. After the distal anastomosis is completed and meticulous de-airing performed, RIVP will be stopped, and the systemic circulation through a side branch of the arch graft will be resumed to perfuse the lower body. Then the arch reconstruction will be carried out by anastomosis of the left common carotid artery, left subclavian artery and innominate artery with the three branches of the arch graft, respectively. ACP will stop, and rewarming will begin. After the anastomosis of the ascending aorta with the graft, the aortic clamp will be removed, and cardiac resuscitation will begin. Patients will be progressively weaned from CPB after the rectal temperature increases above 35.5 °C and the nasopharyngeal temperature reaches around 36.5 °C.

The remainder of the surgical procedure will be performed as standard, including hemostasis and closure of the incisions in layers. Blood components including packed red blood cells, fresh-frozen plasma, and platelets will be infused to maintain the post-CPB hematocrit and correct coagulopathy. Transfusion will be performed if hemoglobin concentration is < 7 g/dL during CPB, < 8 g/dL during surgery or < 9.5 g/dL in the ICU [37]. All patients will be managed in the ICU after the operation.

### Study outcomes

The primary outcome will be a composite of operative mortality and major complications, including paraplegia, postoperative renal failure, severe liver dysfunction, and gastrointestinal complications. Operative mortality is defined as any death that occurs in the same hospital in which the surgery was performed. Other complications will be defined according to the Society of Thoracic Surgery (https://www.sts.org/). The primary outcome will be measured throughout hospitalization (regardless of length of stay) and for up to 30 days after surgery if the patient is discharged. The decision to initiate renal replacement therapy (RRT) will be made by experienced staff in the cardiac ICU. Patients are given RRT if they are classified as grade F according to the RIFLE criteria: serum creatinine ≥ 4 mg/dL or an increase of at least threefold in baseline serum creatinine, or > 75% decline in the estimated glomerular filtration rate. Urine output < 0.3 mL/kg/h for 24 h or anuria for 12 h. We have defined RRT as intermittent hemodialysis or continuous venovenous hemofiltration [38].

Secondary outcomes will include the proportion of patients with a stroke/cerebrovascular incident, paraparesis, postoperative prolonged intubation (> 48 h), temporary neurological deficit, myocardial infarction (MI), acute kidney injury not requiring dialysis, surgical re-exploration for bleeding, and deep sternal wound infection. Patients who require assistance to stand or to walk will be defined as having paraparesis (Tarlov score 3–4) [39]. Temporary neurological deficit [40] will be defined as the occurrence of postoperative agitation, confusion, delirium, obtundation, or a transient focal neurological deficit (resolution within 72 h) without any evidence of new structural abnormality on computed tomography or magnetic resonance imaging. Myocardial infarction [41] will be defined as a rise and/or fall of cardiac troponin values at least one value above the 99th percentile upper reference limit and at least one of the following: symptoms of myocardial ischemia, new ischemic electrocardiogram (ECG) changes, development of pathological Q waves, imaging evidence of new loss of viable myocardium or new regional wall motion abnormality in a pattern consistent with an ischemic etiology, or the identification of a coronary thrombus by angiography or autopsy (but not for type 2 or 3 MI). Prolonged intubation will be defined as a requirement of intubation lasting more than 48 h.

Tertiary outcomes include the length of ICU stay, length of hospital stay, length of endotracheal intubation, volume of perioperative blood product transfusions, as well as total hospitalization cost. The proportion of patients who develop postoperative ascites will serve as a measure of safety in this trial.

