**Methods:**

This study is designed as a multicenter, computer-generated, randomized controlled, assessor-blind, parallel-group study with a superiority framework in patients scheduled for TARS. A total of 636 patients will be randomized on a 1:1 basis to a moderate hypothermia circulatory arrest (MHCA) group, which will receive selective ACP with moderate hypothermia during TARS; or to an RIVP group, which will receive the combination of RIVP and selective ACP under moderate hypothermia during TARS. The primary outcome will be a composite of early mortality and major complications, including paraplegia, postoperative renal failure, severe liver dysfunction, and gastrointestinal complications. All patients will be analyzed according to the intention-to-treat protocol.

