## Methods

### Study design

This study is designed as a multicenter, randomized controlled, assessor-blind, parallel-group study with a superiority framework. Five clinical research centers in China will participate: West China Hospital of Sichuan University, Second Affiliated Hospital of Nanjing Medical University, First Affiliated Hospital of Wannan Medical University, The Second Xiangya Hospital of Central South University, and First Affiliated Hospital of the University of South China.

A total of 636 participants with type A aortic dissection will be randomly assigned by computer to either the MHCA (control) group or the RIVP group at a ratio of 1:1. Patients assigned to the control group will receive selective ACP alone under moderate hypothermia, while patients in the RIVP group will receive selective ACP combined with RIVP under moderate hypothermia. All patients will be admitted to a cardiovascular ICU after surgery, where they will remain until they are considered stable enough to transfer back to a general unit. Postoperative follow-up will be conducted throughout hospitalization (regardless of length of stay) and for up to 30 days after surgery if the patient is discharged, which will be sufficient to show the prognosis of surgical treatment. Patient enrollment began in January 2019 and is expected to be complete within 3 years thereafter. The following members of the study will be blinded to the patients’ group allocation: patients themselves, outcome assessors, and the statistician.

Perfusionists and surgeons in the trial will be experienced in performing the necessary procedures. Interventions will be carried out intraoperatively. Patients’ medical records will be reviewed for in-hospital complications and medication usage.

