### Monitoring of adverse and clinical events

Intraoperative data will include variables linked to the arterial cannulation site for cerebral perfusion (innominate artery, internal carotid artery, axillary artery, or subclavian artery), duration of HCA, CPB time, warming and cooling time, cross-clamp time, surgery time, temperature at the initiation of hypothermic circulatory arrest, concomitant procedures and the application of cross-clamp to the dissected aorta before initiation of hypothermic circulatory arrest, number of units of packed red blood cells, fresh-frozen plasma, pooled platelets and cryoprecipitate administered perioperatively, the highest lactate value during CPB, and the highest flow and pressure of ACP and RIVP.

Patients will be monitored on a daily basis for 7 days after surgery to collect data on temperature, partial pressure of oxygen (PaO_2_) and carbon dioxide (PaCO_2_), inspired oxygen (FiO_2_), ventilation mode, hemoglobin and leukocyte count, and volume of chest drainage. Symptomatic cardiorespiratory complications and other secondary outcome measures (see above) will also be recorded during routine diagnostic tests. These parameters and the timing of notable events will be tracked until hospital discharge.

Patients will be instructed to visit during the hospitalization or following discharge for postoperative data collection. If a face-to-face appointment is not possible, follow-up will be completed over the phone. During each visit, patient characteristics, including mortality, cardiovascular and cerebrovascular events, postoperative renal and liver function, and gastrointestinal complications, will be recorded, Abdominal ultrasound will also be performed at 7 days postoperatively. In addition, radiology and electrocardiography will be performed at each visit after discharge, uploaded to the database and evaluated by outcome assessors blinded to patient allocation.

Preoperative and postoperative data will be recorded by a member of the research team at each participating center who will be blinded to randomization status and who will not be part of the surgical team that performs the interventions. Intraoperative data will be collected by the study perfusionists and anesthesiologists.

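### The mortality component is defined by place of death alone, which conflicts with the day-30 window of the primary outcome and leaves it unsettled whether out-of-hospital deaths by day 30 count

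*Protocol article*

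**What the plan says.** All references are to the protocol article.

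- **Study outcomes, composition.** "The primary outcome will be a composite of operative mortality and major complications, including paraplegia, postoperative renal failure, severe liver dysfunction, and gastrointestinal complications".
- **Study outcomes, definition of the death component.** "Operative mortality is defined as any death that occurs in the same hospital in which the surgery was performed". There is no time limit and no clause for deaths elsewhere.
- **Study outcomes, window.** The primary outcome is measured for the whole hospital stay, however long, and "for up to 30 days after surgery if the patient is discharged".
- **Study design.** Follow-up has the same reach: "for up to 30 days after surgery if the patient is discharged, which will be sufficient to show the prognosis of surgical treatment".
- **Sample size calculation.** The pilot "defined the primary outcome as the abovementioned 30-day composite of operative mortality and major complications".
- **Abstract, Methods.** "The primary outcome will be a composite of early mortality and major complications". No place of death is mentioned.
- **Monitoring of adverse and clinical events.** Visits take place in hospital or after discharge, with telephone contact as a fallback. "During each visit, patient characteristics, including mortality, cardiovascular and cerebrovascular events, postoperative renal and liver function, and gastrointestinal complications, will be recorded".

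**The concern.** The definition turns on where a patient dies, while the window turns on when. For a patient who leaves the operating hospital before day 30 the two rules can give different answers, and nothing in the article says which one prevails.

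Death is the most serious component of the composite. In the pilot it accounted for 4 of 38 control patients (10.5%) and 3 of 38 RIVP patients (7.9%). With a place-based rule, two patients with the same course can be classified differently because one centre transfers or discharges earlier than another, or because two assessors apply different sentences. Five centres take part. If RIVP changes length of stay, time at risk outside the hospital would differ by arm, and so could the number of uncounted deaths. A choice between the two readings made after unblinding could also change the primary result.

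**Working it through.** **1. The two rules side by side**

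| Case | Place definition | Day-30 window |
|---|---|---|
| Dies in the operating hospital, day 15 | counts | counts |
| Discharged or transferred day 12, dies elsewhere day 15, no earlier component event | does not count | counts |
| Same, but renal failure or another component occurred before discharge | primary event already | primary event already |
| Discharged, readmitted to the operating hospital, dies there day 20 | counts | counts |
| Dies in the operating hospital on day 90 without having left it | counts | counts (whole stay is measured) |

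The rules disagree in the second row only. The last row is consistent within the Study outcomes section and is at odds only with the 30-day label in the sample size section.

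**2. The planned sample size reproduces**

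Inputs from the Sample size calculation: p1 = 0.342, p2 = 0.237, two-sided alpha 5%, power 80%, dropout 10%.

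n = (1.960 + 0.842)² × [0.342 × 0.658 + 0.237 × 0.763] / 0.105² = 288.9, so 289 per arm. Then 289 × 1.10 = 317.9, so 318 per arm and 636 in total, as stated. The point here does not touch this arithmetic.

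**3. Illustrative effect on power**

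The documents give no rate of out-of-hospital death by day 30. Below, m is an assumed proportion of control patients who die elsewhere by day 30 with no earlier component event. Evaluable patients: 318 × 0.90 = 286 per arm.

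Power = Φ(Δ/SE − 1.960), with SE = √{[p1(1 − p1) + p2(1 − p2)]/286}.

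Base: SE = √(0.4059/286) = 0.03767; Δ/SE = 0.105/0.03767 = 2.787; power = Φ(0.827) = 79.6%.

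Proportional loss sets p1 − m against p2 − m × 0.237/0.342. Equal loss takes m from both arms.

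| m | Proportional: rates | Power | Equal absolute loss: power |
|---|---|---|---|
| 1 point | 0.332 vs 0.230 | 77.9% | 80.4% |
| 2 points | 0.322 vs 0.223 | 76.2% | 81.3% |
| 3 points | 0.312 vs 0.216 | 74.3% | 82.3% |

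The equal-loss column rises because the difference stays at 0.105 while the variance falls. Both columns assume that 34.2% and 23.7% included these deaths.

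**4. Illustrative effect of a one-sided loss under no true effect**

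True rate 0.342 in both arms, deaths uncounted in RIVP only, 286 per arm. Probability of a significant result favouring RIVP = Φ(Δ/SE − 1.960).

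| Loss in RIVP only | Δ/SE | Probability |
|---|---|---|
| none | 0 | 2.5% |
| 0.5 points | 0.005/0.03960 = 0.126 | 3.3% |
| 2 points | 0.020/0.03937 = 0.508 | 7.3% |

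**The case against.** The strongest reply is that the window sentence shows post-discharge deaths were meant to count. The primary outcome includes mortality, it is measured to day 30 after discharge, mortality is recorded at those visits, and the abstract says early mortality without a place. A reader might infer from the definition that the trial has decided to exclude these deaths. The documents do not support that: the text contradicts itself, and exclusion is one of two readings. What remains is that no sentence adds out-of-hospital deaths to the definition, so the explicit rule and the apparent intention still differ.

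Three further limits stand.

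- **Power.** A reader might infer that the definition costs power in any case. It does not. An equal absolute loss slightly raises power, and a proportional loss matters only if the planning rates included such deaths. The pilot is said to have used the same composite. If it applied the place rule, its rates already leave these deaths out and planned power loses nothing.
- **Bias towards RIVP.** A reader might infer this from the hypothesis of a shorter ICU stay. Leaving the ICU is not leaving the hospital. Length of hospital stay is only a tertiary outcome, and no difference in it is hypothesised in the objectives. The 7.3% figure needs the whole 2-point loss in one arm, against a pilot RIVP mortality of 7.9%. Neither direction nor size is established.
- **Overlap.** Pilot controls had 4 + 1 + 7 + 4 + 1 = 17 component events in 13 patients, and RIVP patients had 3 + 0 + 6 + 1 + 1 = 11 in 9. Patients who die after an earlier component event are counted anyway, so only a subset of out-of-hospital deaths is at issue.

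Counting a late death during an unbroken hospital stay is explicit in the window sentence and is not a fault in itself.

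**Conclusion.** The point holds as a contradiction in the definition of the primary endpoint. The article states the place rule explicitly, so this is not detail left to a fuller document. Applied literally, it leaves one group uncounted: patients who die outside the operating hospital by day 30 with no earlier component event.

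The size is unknown because the documents give no rate for that group. On the assumptions shown, power falls by about 2 to 5 percentage points under proportional loss of 1 to 3 control points, and does not fall under equal loss. The one-sided error favouring RIVP is 3.3% to 7.3%, against 2.5%, if 0.5 to 2 points are lost in RIVP alone. These figures illustrate sensitivity and do not estimate harm. The contradiction does not depend on them. The planned 636 patients reproduce and need not change on this ground.

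**What to change.** Before unblinding:

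1. Define the mortality component as death from any cause within 30 days of surgery wherever it occurs, or later during the index hospitalization.
2. Use that wording in the abstract, Study outcomes and Sample size calculation, and replace the bare 30-day label with the actual window.
3. Ascertain vital status at day 30 for every discharged or transferred patient through the follow-up visit or telephone contact already planned.
4. State whether the pilot rates of 34.2% and 23.7% were obtained under this definition.

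The cost is a one-sentence amendment with matching edits elsewhere. Mortality is already recorded after discharge, so no new data collection is needed beyond making sure that the day-30 contact is complete.
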